## Abstract

**Introduction:**

Tuberculosis (TB) treatment requires the combination of multiple anti-TB drugs during 6 months or more depending on strain drug susceptibility profile. Optimizing the monitoring of anti-TB therapy efficacy is required to provide adequate care and prevent drug resistance emergence. Moreover, accurate monitoring tools are needed for the development of strategies aiming at reducing treatment duration. Opti-4TB is a “proof of concept” study aiming at developing a blood-based monitoring of TB outcome by deciphering host immune signatures associated with latency or disease activity through the combination of “omic” methods. The primary objective is to assess the performances of new biomarkers for TB outcome prediction and to determine specific profiles associated with the outcome of treated TB patients.

**Methods and analysis:**

Opti-4TB is a prospective, single center study including adult patients hospitalized for pulmonary TB. A workflow will be set up to study the immune status of 40 TB patients and 20 controls with latent TB infection. Blood samples will be collected at four timepoints: before treatment initiation (V1), at day 15 (V2), at 2 months (V3) and at 6 months (V4). *Mtb*-specific immune responses will be assessed at each timepoint with three different assays: (1) A whole blood transcriptomic signature assessing the “RISK-6” score; (2) A proteomic signature based on 27 cytokines and chemokines measured in plasma; (3) An immunophenotypic monitoring of circulating T-cell subpopulations using spectral flow cytometry. This in depth characterization of *Mtb*-specific immune response throughout the treatment, correlated with clinical outcomes, will lay the basis for the elaboration of the most basic and universal stage-specific immune signatures associated with latency, active disease and cure.

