In association with the Foundation for Innovative New Diagnostics (FIND), the WHO has set up a series of target product profiles (TPPs) establishing the criteria that these tools should meet in terms of optimal and minimal performance and operational characteristics (7).

The evaluation of biomarkers of the host immune response that correlate with favorable TB outcome is an active area of research. Recently, Zimmer et al. conducted a systematic review and meta-analysis of studies assessing biomarkers for TB treatment monitoring. They identified four biomarkers (CRP, IL-6, IP-10, and TNFα) exhibiting a significant decrease after eight weeks of treatment in several independent studies highlighting the value of these biomarkers for treatment monitoring (8). Studies based on the combination of commercialized IGRAs with an “in-house” IFN-γ release assay based on heparin-binding hemagglutinin (HBHA) stimulation have shown promising results in differencing LTBI from TB patients on whole blood sample (9, 10). Several studies have also confirmed the pivotal role of T-cells and their effector molecules in *Mtb* clearance (11). Modifications in T-cells profiles have been observed between patients with different TB stages. Notably, variations in abundance and phenotypical changes have been found in *Mtb*-specific peripheral CD4+ and CD8+ T-cells subpopulations, as well as MAIT cells among LTBI, active TB, and cured patients (12–17). Recently, based on an in-depth phenotyping with mass cytometry of peripheral *Mtb*-specific T-cells, our group found a differential profile according to sputum conversion. We observed an under-representation of terminal memory effector CD8+ T-cell subpopulations (T_EMRA_) in patients whose sputum cultures were still *Mtb-*positive at two months of treatment compared to patients whose cultures were *Mtb*-negative (18). Successful mycobacterial clearance is linked to CD8+ T-cell effectors, which in turn require CD4+ T-cell engagement (19). Thus, a global evaluation of the anti-TB immune response based on the study of T-cells phenotypic profiles and effector molecules using a peripheral blood-based approach throughout TB treatment might hold the key to overcome the actual limitations in terms of TB treatment monitoring, efficacy and outcome.

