### Objectives

The primary objective of the Opti-4TB project is to assess candidate biomarkers from TB diagnosis to the end of TB treatment:

1) a whole blood transcriptomic signature;2) a whole blood proteomic signature;3) an immunophenotypic signature of circulating T-cells.

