**Box 1:**

Inclusion criteria:
Adult ≥ 18 year-oldPatients having given written consentPatients accepting a follow up ≥ 6 monthsProven active pulmonary tuberculosis (positive direct examination and/or PCR)Or Latent tuberculosis infection assessed by positive IGRA
Exclusion criteria:
Malignant solid tumorMalignant hemopathySolid organ transplantation or hematopoietic stem cell transplantationImmunosuppressive treatments (i.e. biologics, calcineurin inhibitors, corticosteroids)Auto-inflammatory diseaseChronic liver diseasesChronic infection with HIV, HCV (hepatitis C virus) or HBV (hepatitis B virus)Antimycobacterial treatment initiated > 7 daysPregnancy or breastfeedingRefusal to participate to the studyPersons deprived of their liberty by judicial or administrative decisionProtected adultsPatients not affiliated to health-care social securityThe homeless

During the first visit (V1), explanations will be given on treatment duration and schedule of blood sampling occurring at the V1, Day 15 (V2), 2 months (V3) and 6 months (V4) visits to monitor treatment efficacy and tolerance. Additional peripheral blood sampling will be collected at each visit for biomarker assessment as described in Figure 1B.

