### Endpoints

To address the objectives mentioned above, the primary endpoint will be to evaluate the concordance of the kinetics of the biomarkers with the outcome of treated TB patients at each visit. It is a composite outcome including clinical status, radiological computed tomography (CT)-scan assessment and mycobacterial culture conversion of sputum samples.

This will comprise:

1) A whole blood transcriptomic signature based on levels of expression of a panel of 6 genes;2) A proteomic signature based on levels of various cytokines and chemokines production measured in plasma;3) A dynamic phenotypic monitoring of circulating T cell subpopulations through spectral cytometry using a panel of 30 markers;

Secondary endpoints will be to identify profiles, based on the above biomarkers, consistent with three *Mtb* infection stages: LTBI, active TB and cured TB.

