### Study sample size

The main objective of this study is the identification of prognosis factors in terms of treatment efficacy. All the variables of interest represent continuous quantitative variables. Moreover, the distributions of the data for the double IGRA and the immunomonitoring assays are quite asymmetrical requiring non-parametric tests for comparison. For these reasons there is no consensus on the number of participants needed. However, the mean sample size of the studies evaluating biomarkers for TB treatment monitoring recently reviewed by Zimmer et al. was of ~50 patients (8). In addition, reference studies assessing T-cell response in TB patients by immunophenotyping such as Adekambi et al. and Ahmed et al. showed significant T-cell phenotypic changes throughout treatment with cohort of 10 and 39 patients respectively (12, 13). Hence, we expect to include 40 patients presenting active pulmonary TB which is consistent with the number of patients diagnosed yearly in the Infectious Diseases department. We consider that it will allow to obtain statistically significant results. The number of 20 LTBI patients was also chosen according to previous studies (13, 24).

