### Statistical methods

The prognostic power of each biomarker will be evaluated separately. Biomarkers associated with evolution will be kept for multivariate logistic regression models. These models will allow the obtention of different scores per patient and the characteristics of a composite test will be assessed by studying ROC (receiver operating characteristic) curves and calculating AUC (area under the curve). Analysis of the ROC curves will allow estimation of sensitivity, specificity and AUC via mean and confidence interval obtained by bootstraps.

We will study the kinetics of the different biomarkers (clinical, transcriptomic, proteic, or phenotypic) to identify the most basic and universal immune signatures associated with different TB stages: LTBI, active TB and cure.

When required, analyses will be based on two-sided p-values, with statistical significance defined by p < 0.05 and conducted with the software R. Finally, considering multivariate analyses, appropriate multiple imputations will be taken into consideration in case of relevant amount of missing values.

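### V1 is described as a pre-treatment sample, yet Box 1 admits patients already treated for up to 7 days, so the first point of the kinetics may mix untreated and treated blood

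*Protocol article*

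**What the plan says.** The Methods paragraph of the abstract fixes the sampling times as "before treatment initiation (V1), at day 15 (V2), at 2 months (V3) and at 6 months (V4", so V1 precedes treatment.

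Box 1 sets a different limit. Its exclusion list removes patients whose antimycobacterial treatment started more than 7 days earlier. Patients with 0 to 7 days of treatment remain eligible.

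The main text does not settle the matter. The paragraph after Box 1 calls V1 the first visit and gives the "schedule of blood sampling occurring at the V1, Day 15 (V2), 2 months (V3) and 6 months (V4) visits", without saying that V1 comes before the first dose. The Objectives section says the study will "assess candidate biomarkers from TB diagnosis to the end of TB treatment", which fits either reading.

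Two endpoints depend on V1. The primary endpoint is to "evaluate the concordance of the kinetics of the biomarkers with the outcome of treated TB patients at each visit". The secondary endpoints seek profiles for three "infection stages: LTBI, active TB and cured TB".

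**The concern.** A patient who enters on, say, the fifth day of treatment meets Box 1 but cannot supply the sample that the abstract describes. The biomarker blood is additional blood collected at each study visit, and the article describes no route by which an earlier stored sample could stand in for V1.

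V1 anchors each kinetic. If some V1 samples are untreated and others follow several days of therapy, the same visit label covers different biological states, and part of the between-patient variation in early change reflects timing alone. The active TB profile, if built on V1, would carry the same mixture into its contrast with LTBI and cured TB. The first interval is short: with V2 at day 15, a 7-day allowance is 7/15 = 47% of it.

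**Working it through.** The plan has no figure to reproduce here. The 40 TB patients ("we expect to include 40 patients presenting active pulmonary TB") are chosen by precedent, without an effect size or standard deviation. The check is a comparison of the text followed by an illustration.

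**Text comparison**

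| Patient's prior treatment at entry | Eligible under Box 1? | Can V1 precede treatment, as in the abstract? |
|---|---|---|
| None | Yes | Yes |
| 1 to 7 days | Yes | No |
| More than 7 days | No | Not applicable |

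The middle row is the contradiction.

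**What the two possible visit origins imply.** Let L be the days of treatment before V1 (0 to 7).
- V2 counted from the first dose: the V1-V2 interval is 15 − L, which runs from 15 down to 8 days.
- V2 counted from V1: treatment exposure at V2 is 15 + L, which runs from 15 up to 22 days.

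**Share of the true day 0 to day 15 change still visible when L = 7.** All trajectories are assumptions. The Introduction gives a direction only for four biomarkers from a cited review, "exhibiting a significant decrease after eight weeks of treatment in several independent studies", and nothing on the first 7 or 15 days.
- Linear change: (15 − L)/15 from the first dose; 15/15 from V1.
- Exponential decay with half-life h and k = ln 2/h: (e^(−kL) − e^(−15k))/(1 − e^(−15k)) from the first dose; e^(−kL) from V1.

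| Assumed course | V2 counted from first dose | V2 counted from V1 |
|---|---|---|
| Linear | 8/15 = 53% | 100% |
| Half-life 3 days | 17% | 20% |
| Half-life 7 days | 35% | 50% |
| Half-life 14 days | 44% | 71% |
| Half-life 30 days | 49% | 85% |
| Half-life 60 days | 51% | 92% |

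In the exponential rows, the last column is also the share of the baseline excess still present on day 7, and so what a day-7 sample would contribute to an active TB profile.

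With a shorter lead, the effect shrinks. For L = 3 and a 14-day half-life the shares are 74% and 86%. Averaged over a cohort in which half the patients have L = 7 (assumed) and the half-life is 14 days, they are 0.5 + 0.5 × 0.441 = 72% and 0.5 + 0.5 × 0.707 = 85%.

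**A marker that first rises.** Suppose the value is 1.0 at day 0, 1.3 at day 5 and 0.7 at day 15, with straight lines between. The day-7 value is 1.3 − 0.6 × 2/10 = 1.18. The drop to treatment day 15 is 1.18 − 0.70 = 0.48 from a day-7 V1, against 1.00 − 0.70 = 0.30 from a true baseline. Here the early fall is overstated.

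**Later visits, linear change, counted from the first dose.** Taking 2 months as 60 days and 6 months as 180 days, a day-7 V1 keeps 53/60 = 88% of the change to V3 and 173/180 = 96% of the change to V4.

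**The case against.** The strongest reply is that the pre-treatment wording appears only in the abstract, while the body of the article calls V1 simply the first visit. Box 1 permits pre-treated patients; it does not show that any will be enrolled, and V1 might precede the first dose in all of them. The article is condensed, the sampling schedule is in Figure 1B, which is not shown here, and adjustment for days on treatment is commonly left to the analysis plan.

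Much of this stands. The share of pre-treated patients is unknown. The absence of a visit origin in the available text is not a fault of the plan, which is why both origins are worked through above. The lack of a stated adjustment is not a finding on its own.

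The contradiction remains. A 7-day cut-off has a function only if patients already on treatment may enter. If they may, the abstract's description of V1 is not true of all patients; if they may not, Box 1 is too permissive. No other passage in the article reconciles the two.

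A reader might infer more: that early change is understated throughout, that power is lost by a known amount, or that sicker patients start treatment before inclusion, so that the artefact would track outcome. The documents support none of these. The direction depends on the trajectory and the visit origin. No effect size is stated, and no paired V1-V2 test is specified on which to compute power. Nothing links prior treatment to severity.

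**Conclusion.** The concern holds as a contradiction between two stated rules, with a possible effect on the endpoints. V1 may mix untreated samples with samples taken after up to 7 days of treatment.

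Any resulting bias in early change has no fixed sign. It is understatement for markers that fall steadily from the first dose when V2 is counted from that dose. It is nil for linear change counted from V1, and it may be overstatement for markers that first rise. For a steadily falling marker and a day-7 V1, the illustrations run from 17% to 100% of the true V1-V2 change still visible. That range reflects assumed courses, not data from the plan. The contrast between active and cured TB is not necessarily much affected: under linear change 96% of the difference to 6 months survives, and larger losses need short half-lives that the article does not document.

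The contradiction itself rests on the text alone. The use of V1 as the source of the active TB profile is an inference, though the natural one.

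**What to change.** Reconcile the abstract and Box 1 so that V1 has one definition. Which eligibility rule applies is for the investigators to decide.

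If patients already on treatment remain eligible:
- stop describing V1 as pre-treatment;
- record the date of first dose and the date of each sample;
- analyse kinetics by actual days since first dose, not by nominal visit;
- build the active TB profile from samples taken before the first dose, and add the pre-treated patients in a sensitivity analysis.

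The cost is small: a sentence in the protocol, a few dates in an e-CRF that already holds the anti-TB regimen (Variables section), and actual time in place of visit number in the models. The downside is that the untreated active TB profile may rest on fewer than 40 patients. The number of pre-treated patients should be reported, so that a reader can judge how much this matters.

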**Ethics and dissemination:**

Ethical approval has been obtained from the institutional review board (n°69HCL18_0757). Results will be communicated at scientific meetings and submitted for publication in peer-reviewed journals.

**Trial registration number:**

NCT04271397.

## Introduction

Tuberculosis (TB) is a leading cause of death worldwide from infectious disease responsible for approximately 1.5 million deaths yearly (1). Only 5 to 10% of individuals infected with *Mycobacterium tuberculosis* (*Mtb*) will subsequently develop active disease during their lifetime, while the others will have latent TB infection (LTBI). LTBI is detected by interferon (IFN)-γ release assays (IGRAs) such as QuantiFERON-TB (Qiagen®) or T-Spot-TB (Oxford Immunotec®). So far, no test can accurately predict the progression from LTBI to active TB. TB is responsible of a broad spectrum of clinical presentations ranging from minor clinical symptoms to disseminated TB. Lungs are the main disease site accounting for 80% of the cases, although many organs can be affected such as lymph nodes, bones and central nervous system, regardless of lung involvement. TB diagnosis is assessed by the isolation of *Mtb* from patient's specimens either in culture or through molecular methods (2). TB treatment always requires multiple drug regimen administered over a time-period ranging from six to ≥ 18 months, depending on drug susceptibility results. The duration of TB treatment along with related adverse events are the main cause of non-compliance leading to the emergence of multi-drug resistant (MDR)-TB (3).

To date, although sensitivity and specificity are low for predicting failure and relapse, culture conversion of respiratory specimens is still used for treatment efficacy assessment (4, 5). In this context, the World Health Organization (WHO) has adopted in 2015 the “End TB strategy” aiming at reducing the TB-related deaths by 95% and the new contaminations by 90% in 2035 (6). To this end, the WHO encourages the development of new diagnostic and prognostic tools to overcome currently existing tools limitations. The development of these new point-of-care tools should therefore focus on the following objectives:

- to improve the diagnostic sensitivity compared to smear microscopy and sputum culture;- to improve the detection of progression from LTBI to active TB (incipient TB patients);- to accelerate detection of drug resistance to properly guide treatment strategy;- to allow treatment monitoring strategies that provide predictive value for treatment efficacy.

In association with the Foundation for Innovative New Diagnostics (FIND), the WHO has set up a series of target product profiles (TPPs) establishing the criteria that these tools should meet in terms of optimal and minimal performance and operational characteristics (7).

The evaluation of biomarkers of the host immune response that correlate with favorable TB outcome is an active area of research. Recently, Zimmer et al. conducted a systematic review and meta-analysis of studies assessing biomarkers for TB treatment monitoring. They identified four biomarkers (CRP, IL-6, IP-10, and TNFα) exhibiting a significant decrease after eight weeks of treatment in several independent studies highlighting the value of these biomarkers for treatment monitoring (8). Studies based on the combination of commercialized IGRAs with an “in-house” IFN-γ release assay based on heparin-binding hemagglutinin (HBHA) stimulation have shown promising results in differencing LTBI from TB patients on whole blood sample (9, 10). Several studies have also confirmed the pivotal role of T-cells and their effector molecules in *Mtb* clearance (11). Modifications in T-cells profiles have been observed between patients with different TB stages. Notably, variations in abundance and phenotypical changes have been found in *Mtb*-specific peripheral CD4+ and CD8+ T-cells subpopulations, as well as MAIT cells among LTBI, active TB, and cured patients (12–17). Recently, based on an in-depth phenotyping with mass cytometry of peripheral *Mtb*-specific T-cells, our group found a differential profile according to sputum conversion. We observed an under-representation of terminal memory effector CD8+ T-cell subpopulations (T_EMRA_) in patients whose sputum cultures were still *Mtb-*positive at two months of treatment compared to patients whose cultures were *Mtb*-negative (18). Successful mycobacterial clearance is linked to CD8+ T-cell effectors, which in turn require CD4+ T-cell engagement (19). Thus, a global evaluation of the anti-TB immune response based on the study of T-cells phenotypic profiles and effector molecules using a peripheral blood-based approach throughout TB treatment might hold the key to overcome the actual limitations in terms of TB treatment monitoring, efficacy and outcome.

### Rationale

Taking advantage of a range of new whole blood-based methods detecting phenotypical changes of host adaptive immune cells and effector molecules abundance variation, we intend to study their performance in indicating stage-specific profiles associated with TB latency or active disease. We hypothesize that specific detectable immune signatures are associated with LTBI, active TB and cured TB. We will address the question of whether favorable TB disease outcome is associated with immune signature reversion, historically assessed by durable negative smear microscopy and culture conversion.

### Objectives

The primary objective of the Opti-4TB project is to assess candidate biomarkers from TB diagnosis to the end of TB treatment:

1) a whole blood transcriptomic signature;2) a whole blood proteomic signature;3) an immunophenotypic signature of circulating T-cells.

### Deliverables

The Opti-4TB protocol is a “proof of concept” study aiming at developing a blood-based monitoring of TB outcome by deciphering specific host immunity signatures associated with latency, disease activity and cure, through the use of “omic” methods. Currently, there is no prognostic tool to guide treatment and optimize the control of resistance emergence, consistent with WHO priority objectives (pillar 3 of the END-TB strategy). Ultimately, the goal will be to test these host-based signatures in a large multicenter prospective clinical study along with historical standard methods (smear microscopy, sputum culture).

## Methods and analysis

### Study design

The Opti-4TB protocol is a single center prospective “proof-of-concept” cohort study of adult patients treated for drug-susceptible (DS) pulmonary TB at the Infectious Disease Department of a 5362 tertiary care university hospital (Lyon, France). Over the past decade, an average of 30 to 50 patients with culture-confirmed TB were diagnosed and treated yearly in the department.

